## 5. Discussion

The intervention to be assessed in the present study has been developed since 2002 by a team of dieticians, computer programmers, and physicians as the commercial weight management program “SlankeDoktor” [16]. The guiding principle was to improve the cost-effectiveness of established best practice for dietician-supported weight management by using the internet to facilitate interactive communication between the dieticians and the users as well as among the users (peer support through online community). This program was developed iteratively from an initial prototype through trial and error to what is now a well-established commercial product used by 10.000 predominantly healthy overweight or moderately obese users in 2013. Regarding the use in general practice for treatment of obese patients, this program has been tried on a pilot scale with good results [17]. However an appropriately designed randomized controlled trial is required in order to assess the actual cost-effectiveness of this approach compared with other options.

In the Danish health care system, general practitioners are obliged to identify and offer appropriate support to obese patients whose health would benefit from a weight loss, and a prespecified sum per patient is available to finance this support. In most cases this support (“usual care”) consists of 4–6 monthly face-to-face consultations with a health professional, usually a nurse or physician, which includes provision of general weight management information such as brochures and educational internet sites. So the present study has been designed to allow direct comparison between the intervention (dietician-supported internet community) and a single-blind control treatment. The two arms provide the same number of face-to-face consultations which include the sessions to measure and sample the patients. The usual care control treatment will be provided in a way so the patients are not aware which arm they are on by using a placebo website that superficially resembles the interactive treatment without providing any personalized support. This study will utilize the Danish general practice setting, where it is possible to test the combination of face-to-face consultations with dieticians (establishing the relation), real-time online reporting, life style advice, and community peer support as a full scale trial. The online tool in this study will be integrated into the exiting electronic journal system of the general practitioners to emulate how it would be implemented if it was part of the standard offer.

Additional information will be collected from patients and health professionals as feedback to enable further improvements, primarily regarding how to optimize the experience for both patients and health professionals as well as how to identify which patients are most likely to benefit from this type of intervention, in order to optimize resource allocation to this and other options for weight management.

A potential limitation to the chosen study design is that the number of doctors recruited is limited and those who take part might be more interested in new technologies than the average general practitioner. Another weakness of the present study is that the intervention comprises several dimensions of complexity, which preclude evaluation of each aspect of the intervention separately. However, with this new technology doctors will be able to prescribe exercise and diets and obtain insight into patient performance at a much more detailed level than seen before. Compared with other published studies such as [6] the study is a long-term study without monetary incentives for patients, is designed to work in a routine primary care setting, and takes into account the value chain established in the Danish health care system. If the study is successful, this will make it easy to implement the program nationwide and internationally for the benefit of many overweight patients. Additionally the organizational learning provided by this study will be of importance for implementing other medical online support systems in the future and providing new opportunities for the handling of patients in primary care with modern technology and patient empowerment.

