In a recent prospective pilot study without a control group we investigated the effect of a medium intensive online dietician advice combined with a community using the existing commercial online weight loss management program “SlankeDoktor” [16]. We found a mean weight loss from baseline of 7.0 kg (95% CI : 4.6–9.3 kg) after a mean maintenance period of 20 months among 21 patients with an initial BMI of 36.4 kg/m^2^ [17].

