### 3.2. Inclusion Criteria

The patient has a BMI ≥ 30 kg/m^2^.The patient is 18−70 years old.The patient provides informed consent.The patient has home access to the internet.The patient is not pregnant.The patient has no serious or life threatening disease.The patient has no weight loss >3 kg within the last 2 months.

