### 3.5. Control Group

Patients randomized to the control group will receive usual treatment through the medical center, which consists of approximately monthly face-to-face consultations with a nurse or doctor. Additionally they will receive a “placebo treatment” in the form of a login to a website that looks like http://www.praksis.sundhedsdoktor.dk/, but contains only general non-interactive and non-personalized dietary and exercise advice (e.g. “all about diet” from the National Food Agency (Fødevarestyrelsen)), but with neither dietician consultations nor community membership.

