### 3.6. Data

Answers to the standard quality of life questionnaire are collected at the medical center by a nurse at inclusion at 6 months and at 24 months.

Patient characteristics will be entered at the start. Patient height, waist and hip circumference, blood lipids, Hba1c, and weight are measured at inclusion after 6 months and 24 months.

The blood samples will be collected by the bioanalyst in the practice in accordance with guidelines for the handling of blood measurements in Danish general practice and analyzed at the certified laboratory at Odense University Hospital.

Data will be continuously added to a database by the patient, nurse, and dietician.

Number of logins, number of entrances in the different sections of the site, and user patterns will be collected from the database at 6 months and again at 24 months. Dieticians, nurses, doctors, and other health professionals from the medical center will be interviewed about the intervention in relation to their work, their role, their perception of the treatment offered, and the strength and weaknesses seen from their perspective in accordance with the MAST models organizational dimension (Table 1) [18].

In the case of exclusion before the end of the trial, for example, by pregnancy, the patient will if feasible be asked to complete a final questionnaire and have objective parameters measured in order to provide data for an “intention to treat” analysis. The medical centers will be responsible for this. Data and answers to questionnaires will be collected at 6 months and 24 months by independent observers that will assign each patient to a number to mask the identity for the analysts.

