## 4. Statistics

The primary objective of this study is measurement of changes in body weight and waist circumference. Weight loss in the intervention group and control group will be analyzed using appropriate statistical procedures. A weight loss of 5–7 kg in the study group and 2-3 kg in the control group is expected after 6 months of treatment. After 2 years we expect the control group to return to the starting weight, while the study group is expected to maintain a weight loss of 3–5 kg. A power calculation, based on standard deviations observed in a previous pilot project [17], shows that to detect a difference in weight loss of 2.5 kg with a power of 90% requires 142 patients per group. 170 patients will be randomized to each group to allow for dropouts. Secondary outcome such as logins, web site activity, and user patterns will be analyzed in relation to the different quartiles. The most active quartile will be compared to the least active quartile in relation to weight loss, and other measured parameters. If the difference in sustained weight loss after 2 years is greater than 2.5 kg, the planned total of 340 patients will allow analyses of interactions between treatment, gender, age and obesity level. Due to this, the randomization will be stratified by gender, while potential effects of and interactions with other recorded characteristics such as smoking, age and obesity level will be analyzed as continuous or discrete variables as appropriate.

All data will be blinded and the randomization code and identity of the patients will not be revealed to the data manager before analyses are completed. Data will be analyzed by statistical experts. After the study, all data will be made accessible on the internet in anonymized form to allow full peer scrutiny and facilitate secondary research.

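### The listed eligibility criteria do not exclude current users of the commercial programme under test, and no listed measure records its use during follow-up

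*Protocol article*

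**What the plan says.** The Introduction says that the uncontrolled pilot used the existing commercial SlankeDoktor programme, with online dietician advice and a community. Section 5 (Discussion) says that the intervention now to be tested was developed as that programme, and describes it as "a well-established commercial product used by 10.000 predominantly healthy overweight or moderately obese users in 2013".

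Sections 3.2 and 3.3 list seven inclusion and five exclusion criteria. The only one that touches earlier weight-loss efforts is "The patient has no weight loss >3 kg within the last 2 months". None concerns current use of SlankeDoktor.

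Under section 3.5, controls have usual care at the medical centre plus "a login to a website that looks like http://www.praksis.sundhedsdoktor.dk", without dietician consultations or community membership. Section 5 says that patients are not meant to know their arm.

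For use of the intervention, section 3.6 states: "Number of logins, number of entrances in the different sections of the site, and user patterns will be collected from the database", at 6 and 24 months. The questionnaire contains SF12 and further items that are not listed (section 3.3), and is repeated at 6 and 24 months (section 3.6). The limitations named in section 5 do not include contamination of the control arm.

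**The concern.** Most trials of behavioural treatments run some risk that controls find similar help elsewhere. Here the risk is more specific, because the product being tested is already on the market. Its users are described as overweight or moderately obese, which overlaps the trial's population of BMI 30 or more.

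A current subscriber whose weight is stable meets every listed criterion. If randomised to control, that patient already has the online part of the tested treatment. A control who subscribes during the 24 months is in the same position. In the usage data named, both would look like controls who had only the placebo site.

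The effect on the contrast is a bias toward zero. It lowers power and also makes the estimated effect too small. The second matters even when power is ample, because the article says that the trial is to inform cost-effectiveness.

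**Working it through.** **Inputs**
- Section 4: "to detect a difference in weight loss of 2.5 kg with a power of 90% requires 142 patients per group".
- Section 4: "170 patients will be randomized to each group to allow for dropouts". The implied dropout is 1 − 142/170 = 16.5%.
- Section 4: expected 2-year loss of 3–5 kg in the intervention group and a return to starting weight (0 kg) in the control group.
- Not stated: the SD as a number, alpha, and any crossover rate (c). Two-sided alpha 0.05 is assumed, and c is shown over a range.

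**The plan's own figure.** With n per group = 2 × SD² × (1.960 + 1.282)² / 2.5², a value of 142 requires SD = 6.50 kg. Because neither SD nor alpha is stated, 142 cannot be reproduced from stated inputs alone. The pilot's interval (21 patients, 4.6 to 9.3 kg) gives SD = 2.35 / 2.086 × √21 = 5.16 kg, which would need only 90 per group. The dilution calculation below takes the stated 90% power for 2.5 kg as given.

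**Dilution at a true 2.5 kg.** If a share c of controls gains the full effect, the contrast becomes 2.5 × (1 − c). Power is Φ[3.242 × (1 − c) − 1.960], and the evaluable number per group that restores 90% is 142 / (1 − c)².

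| c | Contrast (kg) | Power | Evaluable n per group for 90% |
|---|---|---|---|
| 0% | 2.5 | 90% | 142 |
| 5% | 2.375 | 86.9% | 158 |
| 10% | 2.25 | 83.1% | 176 |
| 20% | 2.0 | 73.7% | 222 |

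**Dilution at a true 3 kg.** The multiplier is 3.242 × 3/2.5 = 3.890.
- c = 10%: Φ(3.501 − 1.960) = 93.8%.
- c = 20%: Φ(3.112 − 1.960) = 87.5%.

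**Margin over 2.5 kg.** From 3 × (1 − c) = 2.5, c = 16.7%. From 5 × (1 − c) = 2.5, c = 50%. Crossover must exceed these values before the contrast falls below 2.5 kg.

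**Partial benefit.** If a subscriber gains half the effect, 10% crossover acts like 5% full crossover: 2.375 kg and about 87% power.

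**Lower SD.** With SD 5.16 kg and a true 2.5 kg, 142 per group would keep 95.7% power at 10% crossover and 90.4% at 20%.

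**The case against.** Several points on the other side have force.

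- **The article is condensed.** A reader might infer that crossover would go wholly undetected. The document does not show this: the questionnaire has unlisted items, and the full protocol is not at hand. What can be said is that no listed measure records it.
- **Access is inferred.** A reader might also conclude that controls can join at any time over two years. The article says only that the product is commercial and gives its user count for 2013. Price, terms and later availability are not described. The intended blinding may also weaken a control's motive to look elsewhere, though it does nothing about patients who already subscribe.
- **The commercial product is not the whole intervention.** Section 3.4 adds up to five dietician consultations and a personal trainer who evaluates exercise, and section 5 adds integration with the practice record system. A subscriber would not get the practice visits, so full benefit is an upper bound.
- **The design has slack.** The expected 3–5 kg against 0 exceeds 2.5 kg, and no document supports any particular crossover rate. This eases the loss of power. It does not remove the bias: full-benefit crossover of 10% shrinks the estimate by 10% whatever the true effect.
- **Former users.** One might argue that past users or pilot patients bring carry-over that biases the contrast. Randomisation balances them between arms in expectation, the pilot had only 21 patients, and the weight-loss criterion removes some recent successful users. This gives no firm reason to exclude all former users.
- **Usual care is the comparator.** In a pragmatic trial, outside help is arguably part of usual care. That supports analysis as randomised, but it does not argue against recording the use.

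**Conclusion.** The point stands in a limited form. The itemised criteria let a weight-stable current subscriber be randomised to control while receiving the online part of the tested treatment, and the named usage data would not show it. The direction of the bias is toward zero; its size is unknown.

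Under the upper-bound assumptions (full benefit, true effect 2.5 kg, two-sided alpha 0.05, 142 evaluable per group), 5%, 10% and 20% crossover give about 87%, 83% and 74% power. At a true 3 kg the figures are about 94% at 10% and 87.5% at 20%.

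The sentence on the commercial product is accurate background and not itself an error, and the documents do not show that crossover will occur or be common. This is an inexpensive improvement, not a fault that undermines the trial.

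**What to change.** 1. Add an exclusion criterion for current use of SlankeDoktor.
2. In the existing 6- and 24-month questionnaires, ask both arms about use of SlankeDoktor or another dietician or online weight programme. If the full questionnaire already has such an item, name it in the protocol.
3. Keep every patient in the arm to which they were randomised, and report outside programme use by arm at both times.

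The cost is the loss of a few otherwise eligible patients and one extra questionnaire item. Excluding all former users, matching trial patients against the commercial user database and estimating a complier-average effect are optional. The first narrows applicability, and the second needs consent and handling of identifiable data.

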### 3.4. Intervention Group

Patients randomized to the intervention group receive a login to the website “http://www.praksis.sundhedsdoktor.dk/” as well as a consultation with a certified clinical dietician within 2 weeks. The website has been developed over a 12-year period with focus groups, usability testing, and user involvement from both patients and health care professionals. At “http://www.praksis.sundhedsdoktor.dk/” the patients fill in a daily diet record as well as their comments, concerns, and questions to the dietician, who will have access to all patient profiles. Patients can monitor and follow their weight loss progress at the website. They have access to a community where they can discuss and chat with other patients and share weight loss experiences as well as give advice and support to each other. Patients receive subsequent 15–30 min consultations with the dietician by appointment at the start and up to every 6 weeks for 6 months to a total of 5 (Figure 2). The certified clinical dieticians also provide individual asynchronous online consultation [14] according to their patients' needs and based on information supplied via the website. The online consultations are weekly during the first 6 months and after that they are monthly. The dietician generates a daily caloric reduction plan of approximately 2400–3200 KJ based on the patients' starting weight, diet record, and physical activity. The dietary advice will be as standardized as possible. In collaboration with the patient goals for obesogenic behavior changes are set up like “eat breakfast every day,” “no late night meal or snack,” and so forth that follow the dietary guidelines given at “http://www.praksis.sundhedsdoktor.dk/” and The Danish Health and Medicine Authority (Sundhedsstyrelsen). A personal trainer evaluates the exercise by monitoring information given by the patients and encourages them to increase their physical activity to a level of at least. Patients will be encouraged to increase their physical activity to a level with at least 30 min daily. Three times a week the physical activity is suggested to be of moderate to high intensity.

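### The patient blinding claimed for this trial is not delivered in the intervention arm and is at best partial in the control arm, so the single-blind and placebo labels should go

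*Protocol article*

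**What the plan says.** Section 5 (Discussion) presents the trial as a "direct comparison between the intervention (dietician-supported internet community) and a single-blind control treatment". It then states that "The usual care control treatment will be provided in a way so the patients are not aware which arm they are on", and gives one mechanism: "by using a placebo website that superficially resembles the interactive treatment without providing any personalized support". The word placebo is also applied to the control website in the Abstract and in Section 3.5.

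Section 3.4 gives intervention patients a login "as well as a consultation with a certified clinical dietician within 2 weeks". Further dietician visits follow "up to every 6 weeks for 6 months to a total of 5". Individual online advice is added: "The online consultations are weekly during the first 6 months and after that they are monthly". There is also a diet record that the dietician reads, a personal trainer who evaluates reported exercise, and a community for discussion and chat.

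Section 3.5 gives controls "approximately monthly face-to-face consultations with a nurse or doctor" and a similar-looking site with general, non-personal content, "with neither dietician consultations nor community membership".

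Masking at other levels is described separately. In Section 3.6, independent observers number the patients so that analysts cannot identify them. In Section 4, the randomisation code is withheld from the data manager until the analyses are finished.

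**The concern.** A website's appearance cannot hide who the patient meets, whether anyone answers, or whether there are peers to talk to. The article therefore asserts a design property that its own description of the arms does not support.

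This matters for what the trial may conclude. The labels single-blind and placebo tell a reader that expectation, disappointment and attention were balanced between the arms. If they carry into the report, a difference will be read as the effect of the programme over and above those influences, when the comparison is of the whole package against usual care with patients largely able to tell what they receive. Control patients who realise that they lack the programme may try less, seek help elsewhere or leave. Self-reported quality of life is open to expectation in both arms. The limitations listed in Section 5 do not mention this.

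**Working it through.** No figure in the article is at issue, so the check sets what each arm receives beside the blinding statement.

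| Feature a patient would notice | Intervention (Section 3.4) | Control (Section 3.5) |
|---|---|---|
| Face-to-face provider | Certified clinical dietician | Nurse or doctor |
| Individual online advice | Weekly for 6 months, then monthly | None; site is not personalised |
| Exercise follow-up | Personal trainer evaluates reports | Not listed; general advice only |
| Peer community | Yes | Expressly withheld |
| Website | Interactive | Non-interactive look-alike |

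**Step 1. What the look-alike site can conceal.** Of the five rows, it addresses only the appearance of the last. The other four are experienced directly.

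**Step 2. Size of the visible difference online.** Taking 6 months as about 26 weeks, and 24 − 6 = 18 months thereafter, the nominal schedule is 26 × 1 + 18 × 1 = 44 individual online consultations in one arm and none through the site in the other. The count is nominal because Section 3.4 also says that this advice follows the patient's needs.

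**Step 3. Blinding by level.**
- Intervention patients: they see the dietician, the replies and the community. Unawareness of arm is not plausible.
- Control patients: they hold a login to a plausible-looking site. If they are not told what the other arm receives, some may not recognise their arm. The patient information is not shown, so at best this is partial concealment.
- Analysts and data manager: masked under Sections 3.6 and 4. Nothing above alters this.
- Outcome assessors: Section 3.6 calls the observers independent and has them mask identity for the analysts. It does not say that they are unaware of arm.

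**Step 4. Which outcomes are exposed.** The Abstract names weight and LDL as primary, and Section 4 names weight and waist. All three are measured. The remaining routes for bias are behaviour in the control arm, unequal dropout, and the self-reported questionnaire that includes SF-12.

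**Step 5. Illustration only.** The article prints neither alpha nor SD. Assuming two-sided 0.05, the stated 142 per group for 2.5 kg at 90% power implies SD = 2.5 / [(1.960 + 1.282) × √(2/142)] ≈ 6.5 kg (about 7.2 kg if one-sided). With SD 6.5 kg, the standard error of the difference is 6.5 × √(2/142) ≈ 0.77 kg. If there were no true effect and a between-arm bias b from knowledge of the arm, the chance of significance is Φ(b/0.77 − 1.96) + Φ(−b/0.77 − 1.96):

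| Assumed b (kg) | Chance of a significant result |
|---|---|
| 0 | 5% |
| 0.5 | about 10% |
| 1.0 | about 25% |
| 1.5 | about 49% |

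The values of b are assumptions. The documents give no basis for choosing one, and the finding does not rest on this table.

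**The case against.** The strongest defence is about scope. The subject of the key sentence in Section 5 is the control treatment, so it can be read as saying only that control patients are not told that theirs is the control. That may work for some of them. This stands, and it is why the control arm is described here as partly concealed and not as unblinded outright. It does not rescue the sentence as a statement about patients in general, nor the single-blind label for the trial.

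The main endpoints are measured, the aim in Section 2 is a comparison with usual care, Section 3.5 puts its placebo term in quotation marks, and the control content is fully disclosed. All of this limits the consequence. It does not make the label correct.

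A reader might infer three stronger things that the documents do not support:

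- *That no blinding exists in the trial.* Analysts and data manager are masked.
- *That the face-to-face counts contradict each other.* Section 5 says that both arms have equal numbers, counting measurement and sampling sessions, and describes usual care as 4–6 monthly visits. This reads naturally as four to six visits at monthly intervals, a range that includes the five in Section 3.4. Section 3.5 gives a frequency without an end. Running it on to 24 visits by month 24 would be the reader's extrapolation, since no section states it. The figure with the consultation schedule is also not shown. What remains is that the equality claim cannot be checked from the text.
- *That patients at one centre will compare notes.* No section addresses this.

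**Conclusion.** The point holds in limited form. The article claims patient blinding that its described arms do not deliver for intervention patients, and that is at best partial for controls. The visible difference comprises a different provider, about 44 nominal online contacts against none, a personal trainer and a community. The share of patients able to identify their arm is not given, and the resulting bias cannot be sized from the documents.

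The randomised comparison and the measured endpoints survive. A reader might go further and treat the weight result as invalid, but nothing in the documents supports that. The harm is to interpretation: a placebo-controlled conclusion, or a blinded reading of SF-12, would be unsupported. The change should be made, but the flaw is not fatal.

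The verdict rests on Sections 3.4 and 3.5 being carried out as written. Unseen patient information could change the degree of concealment among controls, but not the position of intervention patients.

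**What to change.** - In the Abstract, Section 3.5 and Section 5, replace the single-blind and placebo wording with: *open to patients and treating staff; analysts and data manager masked*. Call the control site a non-interactive information site.
- Claim masked outcome assessment only if the independent observers really are kept unaware of arm, and say how. Otherwise state that they are not.
- State that SF-12 and other self-reports are unblinded and will be interpreted as such, and add the lack of patient blinding to the limitations in Section 5.
- Minor: state in Section 3.5 the period over which the control visits run, so that it can be reconciled with Section 3.4 and with the equal-contact statement in Section 5. Record face-to-face and online contacts per patient in both arms, and report equal contact only if the counts show it.

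The cost is mostly wording. Visit counts can come from the practice record. Logins and user patterns are already to be collected at 6 and 24 months (Section 3.6), and Table 1 lists consultation numbers and electronic communication as example organisational measures, though not explicitly per patient. The downside is a less favourable description of the design.

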### 3.3. Exclusion Criteria

The patient fails to complete the initial questionnaire online.The patient becomes pregnant during the study.The patient experiences serious or life threatening disease during the study.The patient moves to another GP practice not participating in the study.The patient has a serious eating disorder or develops one during the study (e.g., rapid weight changes).

Patients will be invited consecutively by doctors and practice staff. The first information is received at the medical center, ensuring full confidentiality. Patients who receive information concerning the study from doctors or practice staff and who agree to participate are registered and scheduled for an appointment with a nurse. The patients will be able to bring a friend or relative in accordance with ethical guidelines for biomedical experiments with humans. An appointment with a nurse is scheduled within 7–14 days after the information; thus the patient has sufficient time to reflect on the decision to participate. The nurse obtains the approved informed consent and proceeds with weighing and measuring the patient. The patient is then instructed to use a web link to a standard quality of life questionnaire including SF12 and other relevant questions from the webpage www.praksis.sundhedsdoktor.dk. Patients are randomized immediately after the questionnaire is filled out, using an automated computer algorithm. This procedure ensures that dropouts can be recorded as well as certain characteristics for the patients who choose to drop out.

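### The protocol claims that patients are blinded by a look-alike website, but the arms differ in ways that no website can hide, so patient blinding cannot be claimed

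*Protocol article*

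**What the plan says.** The protocol article, Section 5 (Discussion), describes the comparator as "a single-blind control treatment" and says that it will be "provided in a way so the patients are not aware which arm they are on by using a placebo website" which resembles the interactive one but gives no personal support. The same paragraph says that both arms have equal numbers of face-to-face consultations.

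Section 3.4 gives intervention patients a website login "as well as a consultation with a certified clinical dietician within 2 weeks", with five dietician visits in total over 6 months. It adds individual online dietician contact: "The online consultations are weekly during the first 6 months and after that they are monthly". Patients also keep a daily diet record and have their exercise followed by a personal trainer. On peer support it says: "They have access to a community where they can discuss and chat with other patients and share weight loss experiences".

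Section 3.5 gives controls usual care, namely "approximately monthly face-to-face consultations with a nurse or doctor", and a general, non-interactive site, "but with neither dietician consultations nor community membership".

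On outcomes, the text under Section 3.3 has patients "instructed to use a web link to a standard quality of life questionnaire including SF12", and Section 3.6 repeats the questionnaire at 6 and 24 months. Weight, waist, lipids and HbA1c are measured at the same times. Sections 3.6 and 4 describe masking of patient identity for the analysts and withholding of the randomization code from the data manager until the analyses are finished.

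**The concern.** The blinding statement covers patients without qualification, and the only mechanism it names is the appearance of a website. Most of what separates the arms lies elsewhere: who the patient meets, whether anyone replies online, what the patient does each day, and whether other patients are there to talk to.

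The label matters because readers use it to judge bias. A trial reported as patient-blinded is taken to be protected against expectation effects in self-reported outcomes. It is also taken to be protected against changes in behaviour by patients who know what they did or did not receive, such as seeking help elsewhere or not returning to be weighed. The limitations paragraph of the Discussion covers the choice of doctors and the complexity of the intervention but does not mention blinding.

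**Working it through.** The question is one of consistency, so the arm descriptions are set side by side. The last column asks whether a look-alike website could conceal the difference.

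| Feature | Intervention (3.4) | Control (3.5) | Hidden by the website? |
|---|---|---|---|
| Face-to-face provider | Certified dietician, first visit within 2 weeks, 5 in total | Nurse or doctor, about monthly | No |
| Number of face-to-face visits | Equal, per Section 5 | Equal, per Section 5 | Matched by design |
| Individual online consultations | Weekly for 6 months, then monthly | None | No |
| Daily diet record for the dietician | Yes | Not part of the control site, which is non-interactive | No |
| Personal trainer follow-up | Yes | Not described | No |
| Peer community | Yes | None | No |
| Look of the site | Interactive site | Similar in appearance | Yes |

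Appearance is masked and the visit count is matched. The other five features differ, and each is something the patient takes part in.

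**Scheduled online contact.** Six months is about 26 weeks, so about 26 weekly consultations. From month 6 to month 24 is 24 − 6 = 18 months, so 18 monthly consultations. Total: 26 + 18 = 44 in the intervention arm, against 0 for controls. This is the nominal schedule; Section 3.4 also ties the online contact to patients' needs. The zero applies to online contact only, since controls do have face-to-face visits.

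**What the described masking covers.** Masking of analysts and of the data manager acts after the data exist. It can protect the analysis. It cannot affect how a patient behaves over 24 months, or how a patient answers the SF-12, where the patient is the assessor.

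**Which outcomes are exposed, and how.** Weight and LDL (primary in the Abstract) and weight and waist (primary in Section 4) are measured, so biased reporting is not the issue for them. The remaining routes are performance bias and differential withdrawal. The SF-12 and other questionnaire items are open to reporting bias as well.

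**The case against.** Five points can be made for the protocol.

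1. *Controls may not know.* Someone who expects an internet programme and receives a login plus regular visits might not recognise this as the control condition. This stands in part. A reader might infer that the trial is fully open-label for every patient, but that depends on what patients were told, and the patient information is not shown. It does not rescue the claim: the protocol describes no restriction on that information, and intervention patients, with a dietician and a community, have little reason to doubt their arm.

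2. *Visit numbers are equal.* This is correct and relevant, because it removes one cue. It leaves the provider and all the online elements unmasked.

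3. *The primary outcomes are measured, and the SF-12 has no stated endpoint role.* This stands and limits the consequences. A reader might infer that the trial's self-reported results would be falsely positive at some calculable rate. The documents give no expected shift, no standard deviation and no between-arm test for the SF-12, so any such rate would merely reflect its assumed inputs.

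4. *Withdrawal is already addressed.* Section 3.6 seeks final measurements, where feasible, from patients excluded early, and Section 4 randomizes 170 per arm for 142 needed, an allowance of 170 − 142 = 28 (28/170 = 16.5%). The first is partial mitigation. The second protects power but does not prevent bias if losses differ between arms. No figure shows that they would differ, so this is a limitation to state, not a demonstrated bias.

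5. *The questionnaire link proves nothing.* A reader might infer that controls are unmasked because every patient is sent to the intervention's web address for the baseline questionnaire. The documents do not say that this link shows any intervention content, nor how the two sites are separated. A shared entry page could equally support the resemblance.

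**Conclusion.** The blinding statement in the Discussion is wrong as written. A website of similar appearance and equal visit counts leave five participant-facing differences in view, including about 44 scheduled individual online consultations against none. Intervention patients can readily recognise their arm. Controls may be partly unaware, but this cannot be established from the article. Patient blinding therefore cannot be claimed; what the documents support is masking of data handling and analysis.

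The conclusion rests on the arm descriptions alone and needs no assumed figure. The documents do not allow the size of any resulting bias to be estimated. The point concerns how the trial is described and interpreted: it does not affect the sample size, the visit schedule, the measured endpoints or their analysis.

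**What to change.** In Section 5:

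- Remove the single-blind label and the statement that patients are unaware of their arm.
- State that patients are not blinded, and that masking applies only to data handling and analysis, as described in Sections 3.6 and 4.
- Describe the control site as a static look-alike information site rather than a placebo, with the same change in Section 3.5 and the Abstract.
- Say that the SF-12 and other self-reported results will be interpreted as unblinded.
- Add performance bias and differential withdrawal to the limitations for weight, waist and LDL.

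Moving the questionnaire to another web page is not warranted by what the documents show. Asking patients at 6 and 24 months which arm they think they are in is not recommended either: by then the guess would be confounded with the weight they have lost, and the question could itself alert controls.

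The cost is a few sentences and a less favourable blinding label. No treatment, visit, measurement or sample-size change is needed.
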